### Outcomes

#### Minor outcome measures

The minor outcome will include healthy people or suspected KD develop into KD, and LKD develops into CKD.

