**Fig. 1 Fig1:**
[figure not shown]
Flow chart of study design

**Table 1 Tab1:** The source of the object of study

Disease-prone areas (case)				Non-ward areas (case)	
Suspected KD (50)	LKD (50)	CKD (50)	Normal ward control (50)	DCM (50)	Normal non-ward control (50)

Moreover, as part of our study design, in-ward and non-ward consultations will be made every 6 months in 2 years to collect baseline data and clinical samples of participants, simultaneously. Whereafter, these data will be uploaded to the confidential database along with the application of a remote diagnosis and treatment system for daily consultation and follow-up of participants.

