#### The follow-up phase

The follow-up events will be conducted by a cardiologist and a nurse (Fig. 1). There will be two types of follow-up, one is a fixed free clinic twice a year, which will be carried out in detail according to the initial stage operation process; the other will be to ask the participant’s recent physical status by phone or WeChat every month (Fig. 1). All the data of follow-up and return visits will be accurately uploaded to the big data platform in a timely and accurate manner. The results will be evaluated and confirmed by three physicians. When the participants will be back in the clinic on schedule, we will inform the patients and interpret the results of the examination and the physician’s assessment reports. However, if the participants will not be able to come to the center due to unavoidable factors, the test report will be sent to them by mail and over the phone consultation by a cardiologist.

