### Study objects

This study will recruit 300 participants among which 200 participants will be from Keshan disease-prone areas in Shaanxi Province and the other 100 participants were from five non-ward areas through a random consultation. This cohort will include the suspected KD (50 cases), LKD (50 cases), CKD (50 cases), normal ward control (50 cases), DCM (50 cases), and normal non-ward control (50 cases) (Table 1). According to our estimation, the final sample size could reach about 300 participants. The recruitment will start from January 1, 2020, to December 31, 2020, and the participants with satisfying eligibility criteria will be included in our study.

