### Eligibility criteria

#### Inclusion criteria

Participants should be between the age of 18 and 70 years old.The participant should have lived in the current place for at least 1 year and have no immigration plan for the next few years.Suspected KD and KD patients will be preliminarily diagnosed and grouped by cardiovascular physicians according to the clinical diagnostic criteria of KD (WS/T 210–2011) and the severity of the disease.Patients with DCM after initial diagnosis will be divided into groups by cardiovascular physicians according to the clinical diagnostic criteria of DCM.

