A professional physician will evaluate the above results. However, it will be further reviewed by a cardiologist to confirm the diagnosis and to recommend any necessary suggestions or requests to repeat the procedure.

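### The stage-change outcome compares readings confirmed by different physicians and pools suspected with healthy participants, so late-confirmed baseline disease may count as incident Keshan disease

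*Protocol article*

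**What the plan says.** The outcome is set under Minor outcome measures: "The minor outcome will include healthy people or suspected KD develop into KD, and LKD develops into CKD". The section gives no rule for telling a new event from a revised baseline reading. Under Data management and analysis, follow-up data go into time-to-event analyses.

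Three places say who settles a participant's diagnosis or results:

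- **Entry** (Inclusion criteria): "Suspected KD and KD patients will be preliminarily diagnosed and grouped by cardiovascular physicians according to the clinical diagnostic criteria of KD (WS/T 210–2011").
- **Baseline visit** (Study visit, The first part): "A professional physician will evaluate the above results", after which "it will be further reviewed by a cardiologist to confirm the diagnosis".
- **Follow-up** (The follow-up phase): "The results will be evaluated and confirmed by three physicians". The same section says the twice-yearly clinic is "carried out in detail according to the initial stage operation process".

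On timing, the Study design section states that "in-ward and non-ward consultations will be made every 6 months in 2 years". On numbers, Study objects states: "This cohort will include the suspected KD (50 cases), LKD (50 cases), CKD (50 cases), normal ward control (50 cases), DCM (50 cases"). The list ends with 50 normal non-ward controls. The Limitations section concedes that KD is hard to tell from dilated cardiomyopathy on clinical symptoms.

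**The concern.** A change of category is the difference between two readings, so it is only as sound as the agreement between the procedures behind them. Two features weaken that here.

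First, the people who confirm are not described in the same way at the two times. A participant's category could change because the readers changed, although the heart did not.

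Second, a suspected case is by definition undecided at entry. If that person had KD all along and is confirmed at a later clinic, the outcome as written is met. This would be so even if identical readers sat at every visit.

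The stake is time order. The Discussion expects the prospective study to help find the causes of KD and to evaluate risk factors for its development. If some converters already had KD when their stool and blood were taken, flora altered by the disease would be presented as preceding it. A marker of existing disease could then be taken for a predictor.

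**Working it through.** **1. Reproduce the stated figure.** Six groups of 50 give 6 × 50 = 300, with 4 × 50 = 200 from disease-prone areas and 2 × 50 = 100 from non-ward areas. This agrees with Study objects and Table 1. Those who can become KD cases under the minor outcome are 50 suspected + 50 normal ward + 50 normal non-ward = 150. A further 50 LKD participants can become CKD.

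**2. Compare the procedures.**

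| Time | Who decides or confirms | Stated criterion |
|---|---|---|
| Entry grouping | Cardiovascular physicians, preliminary | WS/T 210–2011 for suspected KD and KD |
| Baseline visit | One physician, then cardiologist review | Not restated |
| Follow-up clinic | Three physicians | Initial-stage process carried over |

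The visit procedures carry over; the confirming readers do not. How the three physicians combine their views is not stated.

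**3. Late confirmation among suspected cases.** Let q be the share of the 50 suspected cases who already have KD at entry (assumed; the article gives no figure). Up to 50 × q could be relabelled as events: q = 10%, 20% and 30% give 5, 10 and 15.

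**4. Upward re-reading in all 150.** Let r be the false-upgrade rate per reading (assumed). One visit gives 150 × r. Visits every 6 months over 2 years make up to four readings. With independent errors and no reversal of an upgrade, four visits give 150 × (1 − (1 − r)^4).

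| r | One visit | Four visits |
|---|---|---|
| 0% | 0 | 0 |
| 1% | 1.5 | 5.9 |
| 2% | 3.0 | 11.6 |
| 5% | 7.5 | 27.8 |
| 10% | 15.0 | 51.6 |

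A reader's errors on the same person are usually correlated, so the four-visit column leans high.

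**5. Share of counted conversions that are false.** With two-year incidence i and total reclassification r over the same period, both assumed, the share is r/(r + i). It does not depend on the number at risk.

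| r | i = 5% | i = 2% |
|---|---|---|
| 0% | 0% | 0% |
| 1% | 1/6 = 17% | 1/3 = 33% |
| 5% | 5/10 = 50% | 5/7 = 71% |
| 10% | 10/15 = 67% | 10/12 = 83% |

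The table restates its inputs. It shows how sensitive the result is, and is not an estimate.

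**6. Direction of the reader effect.** Assume independent readers with sensitivity 0.80 and specificity 0.95, and a baseline rule that both of two readers must agree.

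- Both of two: sensitivity 0.80² = 0.64; false-positive rate 0.05² = 0.0025.
- Majority of three: sensitivity 3 × 0.80² × 0.20 + 0.80³ = 0.896; false-positive rate 3 × 0.05² × 0.95 + 0.05³ = 0.0073.
- All three: sensitivity 0.80³ = 0.512; false-positive rate 0.05³ = 0.0001.

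A majority rule would make more KD calls at follow-up than at baseline, and unanimity fewer. The change of readers alone could inflate or suppress conversions. The problem in step 3 does not depend on this.

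**The case against.** A fair defence has four parts.

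- **Baseline is more than one physician and a cardiologist.** Inclusion criteria has cardiovascular physicians, in the plural, group suspected KD and KD patients under a named standard. As many clinicians may be involved at entry as later. This stands, and a reader who sees a thin baseline reading set against a full panel goes further than the text.
- **Follow-up follows the initial-stage process.** No change of tests or criteria is stated, and the sentence on three physicians speaks of results without saying that they assign stage. This also stands. It narrows the discrepancy to who confirms, but does not remove it.
- **An article condenses a fuller protocol.** Adjudication rules and masking may be written there, and their absence here is no fault. The point rests on what the article does state: different confirmers, and an outcome that puts suspected and healthy participants under one heading.
- **The numbers are assumed.** A reader might infer that at least half of the conversions would be false. That follows only if reclassification is taken to be as frequent as true incidence or more so. At 1% against 5% the share is 17%, and at zero there is none.

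A reader might also take the minor outcome to be the only part of the study that can show time order. Major outcome measures lists acute attack, severe heart failure and death, which are also observed after baseline sampling.

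**Conclusion.** The concern holds in a limited form. The article describes different confirmation at baseline and at follow-up. Its minor outcome also pools an unresolved diagnosis with healthy people, so revised or late-confirmed baseline disease may be counted as incident KD.

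It would be tempting to say that it will be counted. The documents do not support that: they give no reader agreement, misclassification rate or incidence, and the decision rule of the three physicians is unstated. The size is therefore unknown and the direction of the reader effect is open. The firmer half is the suspected group, where late confirmation satisfies the outcome whoever reads. If 10% to 30% of that group already had KD, 5 to 15 apparent events could come from it. LKD to CKD is exposed to the same change of readers.

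The plan should be changed on this point, but nothing here invalidates the study.

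**What to change.** 1. **Reconcile the text.** Align Inclusion criteria, The first part and The follow-up phase so that one confirmation rule applies at baseline and at follow-up, and state how the physicians reach a decision.
2. **At minimum, re-read the converters.** For each declared conversion, LKD to CKD included, the follow-up physicians read the stored baseline and follow-up records (ECG, ultrasonic cardiogram, BNP) in random order under the barcode, which already carries no group. An incident event counts only if the baseline record does not already meet the later category.
3. **Separate the transitions.** Report suspected-to-KD apart from normal-to-KD. Rest statements about incidence or time order mainly on the normal participants, and describe suspected-to-KD as confirmation or progression.

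This uses physicians and data already in the plan and needs no new visits. Re-reading converters alone costs modest reading time; having the same physicians confirm all 300 baseline records would cost more. The downside is fewer counted conversions, and so less precision for an outcome that may already be rare.

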#### Major outcome measures

The main outcomes will include acute Keshan disease attack, severe heart failure, perioperative period, and death.

### Recruitment

The participants will be informed of the purpose, content, risks, and benefits of this study. If they agree to participate, they should sign an informed consent form and would receive a schedule of this study (Fig. 1). The Clinical Research Center for Endemic Disease of Shaanxi province will review the reported information of participants from time to time via a big data network platform to ensure the orderly arrangement of experimental data.

### Study visit

#### The first part

*Step 1* Collection of baseline data

Blood and stool samples will be obtained from participants to ensure whether they conform to the fasting instructions on the day of the program. Whereafter, the selected participants should sign an informed consent form. The organizer will then assign each participant with a special digital identification barcode. This bar code will be the unique identification of the participants and will accompany them throughout the entire study. However, this bar code will not mention the grouping thus participants.*Step 2* Sample collection

The blood samples will be collected in duplicate (Table 2). One tube of 5 ml (without anticoagulant) will be used to separate the serum for biochemical and mass spectrometry. Whereas the other tube of 2 ml blood (plus EDTA-2k anticoagulant) will be used to separate the plasma for brain natriuretic peptide (BNP) testing. Aliquoted serum and plasma should be stored at − 80 °C.

**Table 2 Tab2:** Data collection using different methods at baseline

Questionnaires	Instruments	Blood sample	Stool
General questionnaire (in 10 sections)	ECG (electrocardiograph and heart rate) UCG (ultrasonic cardiogram) Physical activity questionnaire (IPAQ) Sphygmomanometer (blood pressure)	Hematological parameters (CBC)	Gut flora
Physical activity questionnaire (IPAQ)	Waist, hip, and wrist circumference	Biochemical parameters (total cholesterol, HDL cholesterol, LDL)	
Psychological status questionnaire			
Nutritional habits questionnaire (FFQ based on domestic foods)	Height scale and digital scale for weight	DNA extraction	

*HDL* high-density lipoprotein cholesterol, *LDL* low-density lipoprotein cholesterol

Stool (about 20 g) samples will be collected into an airtight container by the subjects themselves and then divided by the nurse and stored at − 80 °C for mass spectrometry and intestinal microflora analysis (Table 2).*Step 3* A questionnaire survey

After breakfast, participants will fill out a general questionnaire, physical activity questionnaire (IPAQ), psychological status questionnaire, and nutritional habits questionnaire (FFQ based on domestic foods) (Table 2).*Step 4* Functional testing

The parameters including index height, weight, wrist, waist, hip circumference, blood pressure, electrocardiograph (ECG), and heart rate, and ultrasonic cardiogram (UCG) functions will be obtained in this step (Table 2).

A professional physician will evaluate the above results. However, it will be further reviewed by a cardiologist to confirm the diagnosis and to recommend any necessary suggestions or requests to repeat the procedure.

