**Methods:**

This cohort study consists of two parts. Though the first part includes 300 participants, however, recruiting will be continued for the eligible participants. After rigorous screening, the blood samples, stools, electrocardiograms, and ultrasonic cardiogram data would be collected from participants to elucidate the relationship between gut flora and host. The second part includes a prospective follow-up study for every 6 months within 2 years. Finally, deep mining of big data and rapid machine learning will be employed to analyze the baseline data, experimental data, and clinical data to seek out the new biomarkers to predict the pathogenesis of Keshan disease.

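### Step 1 of the study visit, as written, takes blood and stool before consent is signed, which conflicts with the Recruitment section and with Step 2

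*Protocol article*

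**What the plan says.** The order of consent and sampling can be read from four places in the protocol article.

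- **Recruitment.** People are told the purpose, content, risks and benefits. Then: "If they agree to participate, they should sign an informed consent form and would receive a schedule of this study".
- **Study visit, The first part, Step 1.** The step begins: "Blood and stool samples will be obtained from participants to ensure whether they conform to the fasting instructions on the day of the program". The next sentence is: "Whereafter, the selected participants should sign an informed consent form". After that: "The organizer will then assign each participant with a special digital identification barcode".
- **Study visit, The first part, Step 2.** Under its own label for sample collection, the text begins: "The blood samples will be collected in duplicate". It goes on to give tube volumes, the anticoagulant, separation into serum and plasma, the amount of stool, and storage.
- **Abstract, Methods.** "After rigorous screening, the blood samples, stools, electrocardiograms, and ultrasonic cardiogram data would be collected from participants".

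**The concern.** Step 1 uses words of sequence. Samples come first, the signature follows, and the barcode follows the signature. Recruitment and Step 2 imply the reverse order for consent and sampling. A site working from this text has no way to tell which order applies, and one of the two orders draws blood and collects stool from people who have not yet signed.

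The order matters more here than it would for a simple clinical check. Table 2 lists DNA extraction among the uses of the blood sample, and the Background and Discussion describe a biological sample bank kept for later research. For samples with those uses, the plan should leave no doubt that consent precedes collection. Step 1 also restricts the signature to selected participants, which leaves open whether someone could be sampled, not selected, and never asked to sign.

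**Working it through.** There is no figure to reproduce and no formula to apply. The check is to set the stated orders side by side.

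1. **Recruitment:** information, agreement, signed consent, study schedule handed over. Signing accompanies receipt of the schedule, so consent belongs before the scheduled visit. The section does not say in so many words that consent precedes every procedure; that is inferred from where it stands and what it is linked to.
2. **Step 1:** blood and stool obtained, consent signed by the selected participants, barcode assigned.
3. **Step 2:** blood and stool collected, after the consent and barcode of Step 1.
4. **Abstract:** screening, then samples. Consent is not mentioned.

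Comparing these:

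- **Step 1 against Recruitment.** If the signature was given at recruitment, the signature in Step 1 is a second one with no stated purpose. If the signature is given only in Step 1, it comes after sampling. On either reading the text needs correcting.
- **Step 1 against Step 2.** Either sampling has been placed one step too early, or there are two rounds of sampling, of which the one in Step 1 has no tubes, volumes, assays or storage described.
- **Step 1 against its own purpose.** The stated reason for the samples is to verify fasting. A stool sample does not obviously serve that purpose, and asking the participant would.
- **Selected participants.** This can mean people chosen at screening before the visit, or people retained after the Step 1 check. Only the second meaning produces people who are sampled and never sign. The article does not settle which is meant.
- **Separate consent.** No text available for review describes a screening consent that would cover samples taken in Step 1.

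**The case against.** The strongest reply is that this is a fault of wording and not of conduct. Step 1 is labelled as the collection of baseline data, while every operational detail of sampling sits in Step 2, after consent and barcode. The reason given in Step 1 makes little sense for blood and stool, which suggests a garbled sentence about confirming fasting before sampling. The English is imperfect elsewhere in the article too. If Recruitment does precede the visit, everyone attending Step 1 has already been informed and has signed. The flow chart and consent pages are not available for review, and the article condenses a fuller protocol, so a screening consent may exist.

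Much of this stands. It limits what can be said about intent and rules out any claim about what was actually done. It does not remove the conflict: the article does not leave the timing of consent to another document, but states it in two places that do not agree.

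A reader might go further and infer three things that the article does not support.

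- **That samples will in fact be taken from people who have not agreed.** This requires Step 1 to override Recruitment, and nothing says that it does.
- **That the number of such people can be estimated.** That would need a rate of refusal or non-selection after the Step 1 samples. None is given, so any count would simply restate an assumed rate. Saying that all 300 planned participants are affected likewise holds only if Step 1 is carried out literally and nobody signed earlier.
- **That samples would be mislabelled, or that there would be an unexplained gap between people sampled and people analysed.** Both suppose that Step 1 samples are kept. Only the samples in Step 2 are described as stored, and those come after the barcode.

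**Conclusion.** The point holds as an internal inconsistency in the operative methods text. Step 1, as written, puts blood and stool sampling before signed consent and barcode. This disagrees with Recruitment, where consent goes with agreeing to take part, and with Step 2, where sampling comes later. Followed literally, it would mean sampling before signature, possibly including people not later selected. The extent cannot be quantified from the article.

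The conclusion rests on the sequence words in Step 1 being read at face value and on consent at recruitment being understood to precede the visit. Confidence is high that the text conflicts and only moderate as to what was intended. No estimate, sample size or analysis changes. It should be corrected nonetheless, because it governs consent for biological samples and correction is nearly free.

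**What to change.** Reconcile the Recruitment section with Steps 1 and 2 of the study visit by rewording Step 1:

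- information, signed consent and barcode assignment come before any sampling;
- fasting status is checked without taking blood or stool, for example by asking the participant;
- blood and stool are taken only in Step 2.

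If consent is signed at recruitment, Step 1 should only confirm that the signed form is on file. If samples are intended as part of screening, the text should instead say so and state the separate consent that covers them, including for people who are not then selected.

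The cost is rewording one step and the matching site instruction. No procedure is added.

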#### The second part

After accomplishing the first phase, the participants will be informed by the test results or any possible warnings to require a higher medical consultation or other prescription. This free health check and a higher medical consultation will be provided with the motivation to start and continue the research.

